### Definition of datasets analysed

Safety set: All randomised participants who received LiDCOplus monitoring during surgery receive at least one dose of the study drug.

Full Analysis set: All randomised participants, who received LiDCOplus monitoring during surgery and for whom at least death and discharge date are available.

Per protocol set: All participants in the Full Analysis set who are deemed to have no major protocol violations that could interfere with the objectives of the study.

Efficacy will be assessed on both the full analysis set and the per protocol set; not the Intention-to-treat set.

Safety summaries will be performed on the safety set

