**Methods:**

Single-centre randomised controlled parallel group trial. Randomisation by website using computer generated concealed tables. Setting: University hospital in UK. Participants: 128 patients with acute primary hip fracture listed for operative repair under spinal anaesthesia and aged > 65 years. Intervention: Stroke volume guided intra-operative fluid management. Continuous measurement of SV recorded by a calibrated cardiac output monitor (LiDCOplus). Maintenance fluid and 250 ml colloid boluses given to achieve sustained 10% increases in stroke volume. Control group: fluid administration at the responsible (blinded) anaesthetist's discretion. The intervention terminates at the end of the surgical procedure and post-operative fluid management is at the responsible anaesthetist's discretion. Primary outcome: length of acute hospital stay is determined by a blinded team of clinicians. Secondary outcomes include number of complications and total cost of care.

Funding NIHR/RfPB: PB-PG-0407-13073.

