### Randomization and Blinding

Randomisation (on a one-to-one allocation basis) is via a password-protected web based randomisation service provided by the Clinical Trials Support Unit and the sequence not revealed until datalock. To achieve similar numbers and balance on risk, patients will be stratified according to predicted 30-day mortality (2 levels). The Nottingham Hip Fracture Score [22-24], is used to identify patients with low (≤ 10%) or high (> 10%) risk of mortality within 30-days. Subjects are randomised on arrival in the anaesthetic room to minimise the risk of medical or surgical cancellation after randomisation.

Patients, orthopaedic surgeons and ward staff are blinded to the treatment intervention. The operative attending anaesthetist is not blinded to the treatment arm, but is blinded to the cardiac output measurements for the control arm. Postoperative data collection is by a research nurse blinded to treatment allocation. The decision that a patient is medically fit for discharge is made by the multiprofessional team when all are satisfied that the participant has no ongoing needs for acute hospital care. This team is blinded to participant allocation.

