### Measurement of cardiac output

Monitoring of the key cardiovascular variables of blood pressure and cardiac output (volume of blood pumped by the heart per minute) is common in patients at high risk of intra-operative and postoperative complications. One such method employed is the LiDCOplus (LiDCO Ltd, Cambridge, UK). This device allows calibrated, continuous, real-time monitoring of cardiac output on a beat-to-beat basis. The LiDCOplus cardiac output method of measurement is based upon the bolus indicator dilution method of measuring cardiac output, which is the standard method of measuring cardiac output [29,30]. The only equipment required is a peripheral cannula in a vein and an arterial line (a small cannula inserted into an artery that is routinely used in high risk patients).

A small dose of lithium chloride (0.15 mmol) is injected through the venous cannula. This is a very small dose of lithium, which has no known pharmacological effect [31]. Lithium has been used for the measurement of cardiac output for many years without any side effects being reported. A lithium concentration-time curve is measured by withdrawing 5 ml of blood past a lithium sensor attached to the patient's existing arterial line and the monitor then calculates the cardiac output from the area of the primary dilution curve [32,33].

After this initial calibration, beat-to-beat measurements of cardiac output are made by analysing changes in the arterial pressure waveform. The device does not need recalibrating for at least 8 hours [29]. The LiDCOplus monitor provides values for cardiac output, systemic vascular resistance, mean arterial pressure, heart rate and left ventricle stroke volume. These are adjusted for patient weight and height. As measurements of these variables are made on a beat-to-beat basis, the LiDCOplus is an ideal device for measuring changes in cardiovascular variables to interventions such as fluid boluses.

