### Study Intervention

On arrival in the anaesthetic room, all participants have an arterial line sited at the wrist using local anaesthetic and an arterial blood sample taken (to determine sodium and haemoglobin concentrations for calibration of the LiDCOplus monitor). A cannula is inserted into a peripheral vein for calibration purposes and to allow fluid administration, if there is not an adequate one already in place. The arterial line is then connected to the LiDCOplus machine and calibration performed according to the manufacturer's guidelines, using a bolus intravenous injection of lithium [36]. Routine anaesthetic monitoring is instituted by the attending anaesthetist. The spinal anaesthetic is then performed and the patient remains in the anaesthetic room for at least 10 minutes to allow collection the post-spinal anaesthetic data from the LiDCOplus monitor. The patient is then taken into theatre once the anaesthetist is satisfied that the spinal anaesthetic is adequate for surgery.

The management of fluids during the operation differs between the study group and the control group. The control group have the type, amount and rate of their intravenous fluids determined by the anaesthetist, in accordance with their usual practice. The anaesthetist is blinded to the LiDCOplus measurements by placing the LiDCO screen where it is not visible and turning off the arterial waveform display. All intra-operative fluid boluses and drugs administered by the anaesthetist, including timings, are recorded by the Investigator.

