The study group have their fluids given according to the study protocol, based upon LiDCOplus measurements. The participants in this group receive a maintenance fluid of compound sodium lactate solution at a rate of 1.5 ml kg^-1 ^h ^-1^. In addition they may be given 250 ml boluses of a colloid fluid, determined by the LiDCOplus measurements of stroke volume. Fluid boluses are given until the stroke volume to achieve a sustained 10% increase from the baseline (pre-operative) readings. Further boluses are given subsequently should the stroke volume fall by clinically important amounts at any time during the operation (see Figure 1). If the attending anaesthetist feels there are clinical reasons to give more or less fluid they can do so. If blood transfusion is required packed red cells are given as the colloid. Otherwise the colloid given is at the discretion of the anaesthetist. Discretionary actions of the attending anaesthetist are recorded.

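### The safety set depends on a study drug the trial does not have and on monitoring during surgery, so participants exposed only before theatre drop out of the safety summaries

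*Protocol article*

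**What the plan says.** Under Definition of datasets analysed, the Protocol article gives the safety set as "All randomised participants who received LiDCOplus monitoring during surgery receive at least one dose of the study drug". The same section adds: "Safety summaries will be performed on the safety set".

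Elsewhere the article describes what participants actually receive:

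- The abstract names the treatment under test: "Intervention: Stroke volume guided intra-operative fluid management".
- Study Intervention makes the colloid boluses conditional on stroke volume. Apart from packed red cells when transfusion is needed, it leaves the product open: "Otherwise the colloid given is at the discretion of the anaesthetist". For the other arm: "The control group have the type, amount and rate of their intravenous fluids determined by the anaesthetist, in accordance with their usual practice".
- Randomization and Blinding sets the time of randomisation: "Subjects are randomised on arrival in the anaesthetic room to minimise the risk of medical or surgical cancellation after randomisation".
- Study Intervention says that, on arrival there, "all participants have an arterial line sited at the wrist using local anaesthetic and an arterial blood sample taken". The monitor is then calibrated with lithium, the spinal is performed, and only later does the patient go into theatre.
- Measurement of cardiac output describes the calibration: "A small dose of lithium chloride (0.15 mmol) is injected through the venous cannula".

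Two other sections bear on the consequence. Statistics promises a full presentation of all adverse events, and Reporting of adverse events says that all of them will be recorded.

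**The concern.** A safety set should contain everyone exposed to what the trial does to them. This definition fails in two separate ways.

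First, it asks for a dose of something the trial does not contain. Whoever programs the set has to guess what was meant.

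Second, removing that clause is not enough. The remaining condition is monitoring during surgery, but the invasive trial procedures happen earlier. Participants who had the line or the lithium and never reached monitored surgery are exposed and left out. The omission need not be neutral, because trouble with the line or the calibration may itself be why monitoring never reached theatre. At stake are the numerator and denominator of the summarised event rates.

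**Working it through.** **1. Does a study drug exist?** There are two candidates.

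- *Colloid bolus.* It is never called a study drug. It is given only if stroke volume calls for it, and the product is usually the anaesthetist's choice. Control fluids follow usual practice and may also include colloid.
- *Lithium.* It is described only as a calibration indicator, pharmacologically inert at the dose used, and given to both arms.

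Neither is labelled a study drug, so the clause has no referent.

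**2. Order of events** (Randomization and Blinding; Study Intervention):

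| Step | Place | Arms | Enough for the monitoring condition? |
|---|---|---|---|
| Randomisation | Anaesthetic room | Both | No |
| Arterial line, blood sample | Anaesthetic room | Both | No |
| Lithium calibration | Anaesthetic room | Both | No |
| Spinal, then at least 10 minutes of data collection | Anaesthetic room | Both | No |
| Surgery with monitor running | Theatre | Both (screen hidden from the control anaesthetist) | Yes |

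Anyone who leaves the sequence after the second row and before the last has been exposed and is outside the set. The full analysis set carries the same monitoring condition, so the safety set cannot pick up anyone whom the efficacy analysis loses for that reason.

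**3. How many could this be?** The only figure in the document is the drop-out allowance in Sample size and justification.

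Reproducing the plan's own numbers first, with a difference of 3 days, SD 4.9 days, 90% power and α = 0.05 taken as two-sided:

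- Normal approximation: n = 2 × (1.960 + 1.282)² × (4.9/3)² ≈ 56.1, so 57 per group.
- Two-sample t-test: 57.04, so 58 per group. This matches the stated 58.
- Allowance for 10% loss: 58 × 1.1 = 63.8, so 64, as stated. Dividing instead, 58/0.9 = 64.4, so 65. The difference is immaterial here.

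Planned losses:

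- 128 − 2 × 58 = 12 participants, and 12/128 = 9.4%.
- At exactly 10%: 0.10 × 128 = 12.8.

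The ceiling is therefore 12 to 13 of 128. It is not an estimate, for two reasons:

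- Some losses may come before any cannulation or lithium.
- The allowance includes conversion to general anaesthesia, and nothing says monitoring stops then, so converted patients may remain in the set.

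The document gives no split, so the range is 0 to about 13.

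**4. Effect on a summarised rate at the ceiling.** The denominator would be 116 instead of 128, and 128/116 = 1.10. If none of the 12 excluded had an event, the summarised rate would be about 10% too high in relative terms. If events were concentrated among them, it would be too low.

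**The case against.** The strongest reply is that this is a drafting slip with little practical effect. Several parts of it stand.

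- The sentence is ungrammatical. Its intelligible half, monitoring during surgery, recurs in the full analysis set and admits both arms. An analyst would probably ignore the drug clause.
- Membership is decided by participant, not by event. Harm from the line or the lithium in someone later monitored in surgery stays in the summaries, and that covers nearly everyone. Someone whose monitoring was stopped partway through surgery also meets the monitoring condition.
- The line and lithium are common to both arms, and the randomised difference is fluid management during the operation. The between-arm safety comparison is therefore barely touched.
- Randomisation was placed in the anaesthetic room specifically to keep late cancellations few.

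Three stronger readings are tempting, and the document does not support them.

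- *A reader might infer that the set is empty, or that the drug means colloid and the 64 controls are lost.* No section calls colloid a study drug, and the monitoring condition plainly covers controls.
- *A reader might infer a direct contradiction with the promises to record all adverse events and present them in full.* Full listings and summaries on a defined set routinely coexist, so those promises limit the damage and do not conflict with the set.
- *A reader might take 12 to 13 as the number left out.* It is only an upper limit.

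What survives the reply is that the written rule names a non-existent exposure and starts counting after the actual exposures.

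**Conclusion.** The safety set is wrong as stated, and this is not a matter of detail left to the SAP. The drug clause has no meaning in this trial. The monitoring condition excludes participants who had the arterial line or lithium and were cancelled, or had monitoring abandoned, before theatre. Their events should still be recorded and presented. What is lost is mainly their contribution to the summary numerators and denominators.

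The size is unknown, between 0 and about 13 of 128. The upper end assumes that the whole planned drop-out occurs, that every such participant had already been exposed, and that none was monitored in surgery. The efficacy results and the sample size are unaffected. The correction is worth making because it costs almost nothing and the present rule cannot be applied as written.

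**What to change.** Delete the study drug clause and replace the definition with wording such as:

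> *Safety set: all randomised participants in whom any trial procedure (arterial cannulation, lithium calibration or protocol-directed fluid) was started, whether or not surgery or monitoring followed.*

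Report, by arm, how many participants are in this set but were not monitored during surgery, so that the size of the gap is visible.

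The cost is one sentence. Adverse events are already to be recorded, and the Recruitment section gives every participant a follow-up visit the next day, so no new data collection is needed. The change should be made before datalock, while the allocation sequence is still concealed.

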### Selection and withdrawal of participants

#### Recruitment

Participants are identified by their presence on surgical lists and are recruited from the trauma wards. The investigator informs the participant or their nominated representative (other individual or other body with appropriate jurisdiction), of all aspects pertaining to participation in the study. Participation in the study is for the duration of the anaesthetic and surgical procedure, which is approximately two hours. The study intervention is complete at the end of the surgical procedure, though all participants have a follow-up visit the next day to ensure no problems have arisen. The medical notes are reviewed following hospital discharge for in-hospital complications and medication use.

Participants are informed that entry into the trial is voluntary and that they are free to withdraw at anytime without effect on subsequent care. Data on time to discharge and postoperative mortality are collected routinely and separate from this study. These outcome data are therefore available for all randomised participants.

Included in the trial are adults incapable of providing their own consent, since a large proportion of potential subjects will be acutely or chronically confused (around 30%). Exclusion of these patients from the trial would severely limit the applicability of results to clinical practice, since these patients are more likely to die, remain in hospital for longer, and have more complications [22,25-27].

Patients from whom consent cannot be obtained due to a language barrier are not recruited to the study. This is due to the emergency nature of the surgery meaning that it would not be practical to arrange for the provision of translation services. In practice this is a very small proportion of the total elderly population in the study centre.

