### Informed consent

The capacity for consent is assessed routinely by the orthopaedic team, who decide whether the patient is competent to provide consent for the surgical procedure. If they deem the patient is unable to consent for their surgery, then the patient will be deemed incapable of providing consent to enter the study, and assent from their next of kin is sought (or nominated consultee). The capacity for consent may fluctuate in the population being studied. A member of the research team also performs an additional check of the participant's ability to consent, immediately prior to starting the study. All members of the research team are trained at taking consent in accordance with ICH-GCP guidance [28].

All patients are visited postoperatively. If the patient had had a transient impairment of their ability to consent, which has subsequently resolved, retrospective consent is sought from the patient to use their data in the study. If the patient declines, date of discharge and postoperative mortality data are collected as part of routine clinical management and so will be available for analysis. The same would occur if contact with the next of kin pre-operatively had not been possible. If the next of kin subsequently declined assent, the patient data would once again be withdrawn from the study.

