### Sample size and justification

Previous studies of optimisation strategies have demonstrated approximately 30% reduction on acute length of stay or time until medically fit to discharge and approaches towards 50% reductions in complications in survivors.

Length of acute hospital stay in our unit is consistently around 17 days (SD 4.9 days), so to find a 3 day reduction in LOS in survivors would require 58 patients in each group with 90% power and α = 0.05. Assuming a 10% drop out rate (conversion to general anaesthesia, operative cancellation after randomisation etc.) we aim to randomize 64 subjects in each group. This would also provide the same power to find a 50% reduction in complication rates between the two groups. The study will not be powered to demonstrate differences in mortality (a 50% reduction in 30-day mortality from 10% to 5%, would require around 450 patients in each group).

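### Efficacy is analysed only in patients monitored during surgery, and intention-to-treat is ruled out, although discharge and death dates are held for everyone randomised

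*Protocol article*

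**What the plan says.** Definition of datasets analysed (protocol article) gives two efficacy sets and rejects a third: "Efficacy will be assessed on both the full analysis set and the per protocol set; not the Intention-to-treat set".

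- The wider of the two, called the full analysis set, is defined like this: "All randomised participants, who received LiDCOplus monitoring during surgery and for whom at least death and discharge date are available".
- The narrower one, for the per protocol analysis, is cut down from it by judgement: "All participants in the Full Analysis set who are deemed to have no major protocol violations that could interfere with the objectives of the study".

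Four other parts of the article bear on this.

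- **Recruitment**, on the outcome data: "Data on time to discharge and postoperative mortality are collected routinely and separate from this study". From this the section draws a conclusion that matters here: "These outcome data are therefore available for all randomised participants".
- **Randomization and Blinding** places randomisation at arrival in the anaesthetic room and adds: "The operative attending anaesthetist is not blinded to the treatment arm". The anaesthetist is blinded only to the monitor readings of control patients.
- **Study Intervention** puts the arterial line, calibration and spinal anaesthetic in that same room, before transfer to theatre, for both arms.
- **Sample size and justification** allows for loss: "Assuming a 10% drop out rate (conversion to general anaesthesia, operative cancellation after randomisation etc". It sizes the trial on length of stay in survivors.

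**The concern.** Randomisation makes the arms comparable as allocated. A set defined by something that happens afterwards keeps that protection only if the event is unrelated to arm, or if those removed have the same outcomes as those kept. Monitoring during surgery is such an event.

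The usual reason for leaving patients out is that their outcome is unknown. On the article's own account that reason is absent for discharge and death dates. If the dates exist for everyone, the date requirement in the full analysis set removes nobody, and the monitoring requirement does the excluding. The plan would then set aside patients whose length of stay it holds.

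At stake is which patients enter the primary comparison. If patients with long stays were lost mainly from the intervention arm, the benefit would be overstated; if mainly from the control arm, it would be understated. This is a rule the article states, not a detail left to an analysis plan.

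**Working it through.** **Inputs from Sample size and justification:** SD 4.9 days, target difference 3 days, α = 0.05 (taken as two-sided), 90% power, 58 per group, 10% drop-out, 64 randomised per group. **Assumed, not in the documents:** how loss divides between arms, and how much longer excluded patients stay.

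**1. The plan's own figure.** Normal approximation: n = 2 × (1.960 + 1.282)² × (4.9/3)² ≈ 56.1, rounded up to 57 per group. The t-test solution is 57.04, rounded up to 58. The stated 58 reproduces. For drop-out, 58 × 1.10 = 63.8, so 64 (dividing by 0.90 gives 65).

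**2. Scale of the allowance.** 10% of 64 is 6.4 per arm; 10% of 128 is 12.8 in all. This covers loss from all causes and is not stated to be the exclusion rate of the full analysis set.

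**3. Shift in the difference.** Let f be the fraction excluded from an arm and D the mean stay of those excluded minus that of those kept. Exclusion moves that arm's mean by f × D. With the same D in both arms, the difference moves by (f₁ − f₂) × D.

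| Loss in the two arms | D = 3 days | D = 8 days |
|---|---|---|
| 10% and 0% | 0.30 | 0.80 |
| 10% and 5% | 0.15 | 0.40 |
| 10% and 10% | 0 | 0 |

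The top row is 0.3/3 = 10% to 0.8/3 = 27% of the target.

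**4. Effect on false positives.** With 64 and 57.6 patients the standard error is 4.9 × √(1/64 + 1/57.6) = 0.89 days. With no true effect, a shift of 0.3 days raises the two-sided error from 5% to about 6%, and 0.8 days to about 15%. These figures are in untransformed days; the planned analysis uses log length of stay.

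**5. Price of analysing everyone as allocated** (t-test, SD 4.9).

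- Planned set: 64 × 0.90 = 57.6 per arm, 3 days: 90.3% power.
- All 64 per arm, 10% showing no effect, so 0.90 × 3 = 2.7 days: 87.1%.
- All 64 per arm, full 3 days: 93.0%.

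The cost in the diluted case is 90.3 − 87.1 = 3.2 points.

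**The case against.** The strongest reply is that the exclusion rule is the same in both arms. Every participant gets the arterial line, calibration and monitor, and treatment differs only in fluid management during the operation, so losses before theatre precede any difference in treatment. Some cancellations will be surgical, and the article does not say who decides that monitoring is abandoned or that a patient is excluded. All of this stands. Differential loss is possible, not shown.

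It follows that several stronger readings are not supported.

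- A reader might infer that the full analysis set loses 10%. A patient converted to general anaesthesia with the monitor still running meets its definition, so the drop-out allowance is not its exclusion rate.
- A reader might infer that per protocol violations must fall mainly on the intervention arm, because only that arm has a fluid protocol. But Study Intervention lets the anaesthetist give more or less fluid there on clinical grounds, so such departures are not clearly violations, and controls can depart from protocol too.
- A reader might see a contradiction in Informed consent, where routine data survive a patient's refusal but "If the next of kin subsequently declined assent, the patient data would once again be withdrawn from the study". The sentence can be read as one rule, with study data withdrawn and routine dates kept. It is an ambiguity about consent and does not bear on this point.

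A further objection limits the remedy. The Recruitment section promises discharge and death data only. The Statistics section names time until medically fit for discharge as the primary measure, and nothing says that date is routinely held for unmonitored patients. This also stands, and the fix allows for it.

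None of this explains why the intention-to-treat set should be ruled out when the dates for acute length of stay exist.

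**Conclusion.** The point holds as a risk the plan accepts without need. The efficacy sets depend on a post-randomisation event, in a trial whose attending anaesthetist knows the arm, and the set that would avoid this is excluded in words.

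The size of any bias cannot be taken from the documents. The 0.3 to 0.8 days rests on two assumptions: 10% lost from one arm and none from the other, and an excess stay of 3 to 8 days. Partly balanced loss gives proportionately less, and equal loss of similar patients gives none. A reader might conclude that randomisation no longer protects the comparison; the text supports only that the comparison can be biased.

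The change is still worth requiring. It settles who enters the primary comparison and costs about 3 points of power. The article describes recruitment as ongoing, plans no interim analysis and withholds the sequence until datalock, so the rule can be changed before results are known.

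**What to change.** Replace the sentence rejecting intention-to-treat with wording such as: *The primary efficacy analysis includes all randomised participants in the arm to which they were allocated. The full analysis set and the per protocol set are used for sensitivity analyses.*

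Three details need settling with it.

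1. **Acute length of stay** (the primary aim under Study Objectives): apply the new set using the routine discharge and death dates.
2. **Medically-fit date** (the primary measure in the Statistics section): confirm that it is recorded for randomised patients who were not monitored. If it is not, start collecting it and report how many are missing by arm.
3. **In-hospital deaths:** state how they enter the length-of-stay analysis. The sample size refers to survivors, and survival is itself a post-randomisation condition.

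**Cost.** A paragraph of wording, and no new data for acute length of stay; the medically-fit date may need extra collection. The estimate is slightly diluted: about 87% rather than 90% power if 10% show no effect. Restoring 90% in that case would take about 70 per group (70 by normal approximation, 70.2 by t-test), but the correction does not depend on enlarging the trial.
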